### Health Economic Analysis

We will develop a simulation model to assess the potential cost-effectiveness of the e-mhGAP-IG compared with the paper-based tool. We are not measuring patient outcomes within the study; hence, costs of services and impacts on patients will be taken from other sources. The model will take the form of a decision tree that maps out key events following the use of either tool and outcomes that are achieved. A simple form of the model will have cases detected or not as key events and whether or not outcomes improve as a result of detection (the latter information coming from previous research). The cost of providing care for people detected will be included as will the reduction in disability-adjusted life years (DALYs) following treatment. Some of the data will be obtained from within the study (costs of using the tools based on staff time and rate of detection of depression), whereas other data (costs of treatment and DALYs) will be obtained from the wider literature and expert opinion. The model will be subject to sensitivity analyses to address the uncertainty of the model parameters. The model will enable us to generate a cost per DALY avoided by using the tool.

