#### PCW and Patient Outcome Analysis

The primary outcome will be the accuracy of the depression diagnosis. The research team will identify a patient as screening positive based on the PHQ-9 result immediately before or after the patient sees the PCW. *Screening positive* will be defined as scoring  $\geq 10$  on the PHQ-9. The research team will also assess sensitivity to change, for change in both the PHQ-9 and WHODAS 2.0 scores from baseline and 3 months after initiation of treatment. *Positive diagnosis* will be defined as a clinical diagnosis of depression documented by the health worker in the clinical notes. *Accurate detection* will be defined as PHQ-9  $\geq 10$  and a health worker depression clinical diagnosis. We will also report findings in terms of the sensitivity and specificity of health worker diagnoses. *Sensitivity* will be defined as the proportion of health worker–diagnosed patients who had PHQ-9 above the cutoff, out of all patients who scored above the PHQ-9 cutoff. *Specificity* will be defined as the proportion of patients who did not receive a health worker depression diagnosis and scored below the PHQ-9 cutoff, out of all patients scoring below the PHQ-9 cutoff.

Features of the cRCT design will be accommodated in all analyses, and an intention-to-treat approach will be used. The principles of analysis will be (1) the PHC-level accuracy outcome is binomial (ie, number of accurate diagnoses out of all diagnoses based on patient-level data), and therefore, a generalized linear mixed model will be used (specifically, a log-binomial regression to obtain probability ratios); (2) accuracy is a cumulative measure, and therefore, there are no repeated measures over time; and (3) missing data can occur at either the health worker or patient level.

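### The cost-effectiveness tree has no branch for patients diagnosed with depression who do not have it, so cost per DALY cannot respond to a specificity difference between the two tools

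*Protocol*

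**What the plan says.** The Health Economic Analysis section of the protocol fixes five features of the model.

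- **Events:** "A simple form of the model will have cases detected or not as key events", followed by whether outcomes improve because of detection. The improvement information comes from previous research.
- **Care cost and benefit:** "The cost of providing care for people detected will be included as will the reduction in disability-adjusted life years (DALYs) following treatment".
- **Inputs from the study:** "costs of using the tools based on staff time and rate of detection of depression". Treatment costs and DALYs come from the literature and expert opinion.
- **Uncertainty:** "The model will be subject to sensitivity analyses to address the uncertainty of the model parameters".
- **Output:** "The model will enable us to generate a cost per DALY avoided by using the tool", with the e-version compared with paper.

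The PCW and Patient Outcome Analysis section defines accurate detection as a PHQ-9 score of 10 or more together with a PCW diagnosis, and separately defines a positive diagnosis as any documented one. It adds: "We will also report findings in terms of the sensitivity and specificity of health worker diagnoses". Specificity there is taken over patients below the PHQ-9 cutoff. The Technology section names inaccurate diagnosis and overmedication among the problems that the dashboard should help supervisors to spot.

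**The concern.** A diagnostic aid can raise detection partly by raising the number of diagnoses overall. Some of the extra diagnoses fall on people without depression, who use care but have no depression-related DALYs to avert. A model comparing two such aids needs somewhere to put them. This tree has no such place: its events concern cases only, and specificity is not among its inputs even though the trial will report it. Sensitivity analyses that vary parameters cannot supply a missing branch.

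At stake is the e-version versus paper comparison. If the tools differ in specificity, the model ignores the difference, and the error favours the tool that over-diagnoses more. At the prevalences the protocol quotes, 83% to 95% of patients are not depressed, so a small specificity difference moves many people.

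**Working it through.** The protocol states no cost-effectiveness result, so there is no figure to reproduce. The check asks how far the tree's output would move if false-positive care were costed.

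**Inputs from the protocol**
- Prevalence *p*: 16.8% among primary care attenders in Nepal and 5.5% in Nigeria (Settings). The Nigerian figure is not stated to be for attenders.
- Detection: 10% and 53% (Statistical Power and Sample Size Calculation). There they are before-and-after values within an arm. Using them as paper versus e-version is an assumption.

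**Assumed, not in the protocol**
- False-positive rate (FPR) of 5% with paper, and 2%, 5%, 10% or 20% with the e-version.
- The same care cost for every diagnosed patient, the same benefit per true case detected, and no tool-cost difference.

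**Formula.** Let ΔTP and ΔFP be the extra true and false positives with the e-version. The tree gives an incremental cost per DALY proportional to ΔTP/ΔTP. Full costing gives (ΔTP + ΔFP)/ΔTP. The ratio of the two is

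1 + [(1 − p)/p] × (FPR difference)/(detection difference).

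**Main case, per 1000 patients, FPR 5% v 10%**
- p = 16.8%: true positives 16.8 v 89.04, so ΔTP = 72.24. False positives 41.6 v 83.2, so ΔFP = 41.6. Ratio = 113.84/72.24 = 1.58.
- p = 5.5%: true positives 5.5 v 29.15, so ΔTP = 23.65. False positives 47.25 v 94.5, so ΔFP = 47.25. Ratio = 70.90/23.65 = 3.00.

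**Range, paper FPR 5%**

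| e-version FPR | Detection, paper v e-version | p = 16.8% | p = 5.5% |
|---|---|---|---|
| 2% | 10% v 53% | 0.65 | −0.20 (net care-cost saving) |
| 5% | 10% v 53% | 1.00 | 1.00 |
| 10% | 10% v 53% | 1.58 | 3.00 |
| 20% | 10% v 53% | 2.73 | 6.99 |
| 10% | 30% v 53% | 2.08 | 4.74 |

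The tree as described returns 1.00 in every row.

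**If everyone diagnosed counts as detected.** Let each diagnosed patient carry care cost *c* and DALY gain *d*. The increment is then c(ΔTP + ΔFP)/[d(ΔTP + ΔFP)] = c/d, which again does not depend on specificity. With a positive tool-cost difference, extra false positives would even lower cost per DALY, because that cost is spread over DALY gains that do not occur.

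**Reference standard.** The trial measures against PHQ-9 of 10 or more, not depression itself. From the PHQ-9 sensitivity and specificity given under Patient Data (94% and 80% in Nepal, 85% and 99% in Nigeria), the screen-positive share would be:
- Nepal: 0.168 × 0.94 + 0.832 × 0.20 = 32.4%
- Nigeria: 0.055 × 0.85 + 0.945 × 0.01 = 5.6%

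Putting these in place of *p* in the main case gives 1 + (0.6757/0.3243) × (0.05/0.43) = 1.24 and 1 + (0.9438/0.0562) × (0.05/0.43) = 2.95.

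Some patients below the cutoff do have depression:
- Nepal: 0.168 × 0.06/(0.168 × 0.06 + 0.832 × 0.80) = 1.5%
- Nigeria: 0.055 × 0.15/(0.055 × 0.15 + 0.945 × 0.99) = 0.9%

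If PCWs diagnose 10% of those below the cutoff, at most about 15% (Nepal) or 9% (Nigeria) of these apparent false positives can truly be depressed. If they diagnose 5%, the limits are about 30% and 17%.

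**The case against.** **The structure is not final.** The protocol speaks of a simple form of the model, and branch detail is often left to an analysis plan. That is fair as far as it goes, and a fuller form is not excluded. But none is described, and the section goes beyond silence: it states the events, the costs counted and the study inputs.

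**The wording on detected people may include everyone diagnosed.** Because the protocol defines accurate detection separately, the unqualified term could be wider. The care would then be costed, and the node for improvement could in principle carry non-improvement. But improvement is to come from previous research, and no separate value is named for people without depression. As written, they would share in the DALY reduction.

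**The size is assumed.** This stands. The document gives no PCW specificity and nothing to show that it differs between arms. The detection contrast is borrowed from a before-and-after example, and the Nigerian prevalence may not apply to attenders. A positive tool-cost difference would shrink the ratios.

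**PHQ-9 below 10 is not absence of depression.** This also stands. Giving every such patient zero gain would be an error of its own, though a bounded one, so the fix must allow for it.

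**A tempting stronger reading.** A reader might infer that cost per DALY is biased downward for both tools. The document does not support that. The model compares the two tools with each other, so false-positive care cancels when specificity is equal and the error can run either way. A single tool's average care cost per true case does rise once false positives are counted, but that is not the incremental output the protocol promises.

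**Conclusion.** The point holds as a structural flaw in the described model. On either reading of what it means to be detected, no patient carries care cost without depression DALY gain, so the incremental cost per DALY cannot register a specificity difference. With equal specificity there is no distortion. Otherwise the result flatters the tool with more false positives, which could be the e-version or paper.

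Under the main assumptions, full costing gives about 1.6 times the tree's figure at 16.8% prevalence and 3.0 times at 5.5%. If the e-version were the more specific, full costing would give a lower figure. These sizes are illustrative. The insensitivity and the direction of the error do not depend on them.

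A reader might also infer that the plan favours the e-version. Nothing in the document shows which tool is the less specific. The change is worth making but not critical: this is a secondary modelling exercise in a feasibility trial, and cost-effectiveness appears neither among the numbered objectives nor among the progression criteria.

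**What to change.** 1. Add two branches for patients without depression: diagnosed (false positive) and not diagnosed (true negative).
2. Populate them with the specificity observed in each arm. The protocol does not say that specificity will be reported by arm, but the diagnosis and PHQ-9 data it needs are already collected in clinics whose allocation is known.
3. In the base case, give false positives care cost and no depression DALY gain.
4. In sensitivity analyses, vary specificity by arm and the share of diagnosed patients with PHQ-9 below 10 who truly have depression. Use the protocol's PHQ-9 accuracy figures to set the range.
5. State whether detected means any PCW diagnosis or a diagnosis with PHQ-9 of 10 or more, and use that meaning for both costs and benefits.

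The cost is slightly more modelling work and no new data collection. The cost per DALY may become less favourable.

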## Study Arms

### Intervention Condition

The intervention will consist of (1) availability of the adapted e-mhGAP-IG for use on a clinic tablet, (2) participation in remote supervision and the support module developed in phase 1 for implementation in Nepal and Nigeria, and (3) training to all relevant PCWs and supervisors in the use of the adapted e-mhGAP-IG and clinical dashboard. Health care providers with enhanced mental health knowledge who have attended the training of trainers workshops for the e-mhGAP-IG and remote supervision will act as supervisors for the purpose of the study. These might include, but are not limited to, psychiatrists, mental health nurses, general physicians, senior PCWs, and counselors.

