5. Integration and sustainability: The potential for long-term integration of the mhGAP-IG v2.0 within standard health services will be assessed using the NoMAD (Normalization Measure Development) scale [38,39]. NoMAD is a 23-item instrument that assesses staff perceptions of factors relevant to embedding interventions in health care. NoMAD consists of 4 theoretical constructs: (1) coherence, (2) collective action, (3) cognitive participation, and (4) reflexive monitoring.
6. Operating costs: The time taken to be trained and to use the paper and electronic tools and for remote supervision will be estimated from information collected from staff, and this, combined with information on staff wages, will be used to derive operating costs for the economic modeling.

During the last data collection time point (PCW3), 15 PCWs in each country will be randomly selected and invited to participate in an additional qualitative interview with a member of the research team to gain further insight into their views on the implementation of the mhGAP-IG v2.0

and remote supervision. We will aim to conduct focus group discussions (FGDs) in the first instance. However, where this is not possible, individual interviews will be conducted. Individual interviews and FGDs will be audio recorded and last no longer than 30 and 60 minutes, respectively. The interviews will be transcribed and anonymized before analysis.

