5. Suicidal ideation and behavior: Suicidal ideation and behavior will be assessed, in Nepal only, using suicidality questions adapted from the Composite International Diagnostic Interview suicidality module [57]. This tool has been widely used in Nepal [58]. We will ask participants whether they had thought of taking their own life in the past 12 months. Those who will respond affirmatively to the ideation question will be asked if they had made a plan to take their own life. In Nepal, those who meet the criteria for current suicidal thoughts or those who attempted suicide in the past 3 months will be immediately referred to a trained psychosocial counselor. In Nigeria, patients endorsing the suicidal ideation item from the PHQ-9 will receive further assessment of suicide risk in line with local protocols.

Confirmation of diagnosis and treatment initiation will be collected from the clinical notes by PCWs. Patients interviewed in the first 3 months of data collection and who screen positive for depression will be invited to participate in a follow-up interview 3 months after their first appointment. The interview will consist of quantitative assessments of depression (PHQ-9), disability (WHODAS 2.0), therapeutic alliance (the ENACT-service user version), and suicide ideation and action Composite International Diagnostic Interview. Treatment details will be extracted by the research team from patient records to document treatment retention.

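### As written, the economic model costs each tool from staff time and wages only, so the tablet, app and dashboard supplied only to the electronic arm are left out and the cost per DALY leans towards the e-version

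*Protocol*

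**What the plan says.** **Tool cost.** Protocol, Implementation Data, PCWs Data, item 6, on operating costs, fixes the resource to be measured: "The time taken to be trained and to use the paper and electronic tools and for remote supervision will be estimated". Staff supply the figures. The valuation follows: "this, combined with information on staff wages, will be used to derive operating costs for the economic modeling". Health Economic Analysis repeats this, naming as the data from within the study "costs of using the tools based on staff time and rate of detection of depression". On outside sources it says that "other data (costs of treatment and DALYs) will be obtained from the wider literature and expert opinion". The output is an incremental cost per DALY for the electronic against the paper tool, with sensitivity analyses on the model's parameters.

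**What each arm receives.** Intervention Condition begins with "availability of the adapted e-mhGAP-IG for use on a clinic tablet" and adds training in the app and the clinical dashboard. Table 1 ticks the electronic guide and both dashboard-training rows for the intervention arm only. It ticks the paper guide for both arms, and its footnote keeps paper available to the intervention arm for the whole study. Remote Supervision describes project phones and data packages without limiting them to one arm.

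**Patient outcomes.** Health Economic Analysis states: "We are not measuring patient outcomes within the study; hence, costs of services and impacts on patients will be taken from other sources". Patient Data under Outcome Data describes a follow-up interview 3 months after the first appointment: "The interview will consist of quantitative assessments of depression (PHQ-9), disability (WHODAS 2.0), therapeutic alliance", with treatment details extracted from records.

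**The concern.** A comparison of a digital tool with a paper one should cost what distinguishes them. Here the named inputs cover what the arms have in common in kind (staff hours, treatment, DALYs) and none of the hardware, software or hosting that only the electronic arm needs. The model would then understate the extra cost of the e-version. The planned sensitivity analysis would not reveal this, because it varies parameters that are in the model, and an item left out is not one of them.

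What is at stake is the first estimate of potential cost-effectiveness. The Objective in the Abstract names the cost-effectiveness comparison as an aim of the later, fully powered trial.

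The sentence about patient outcomes is a second, separate problem in the same section. It is offered as the reason for taking patient impacts and service costs from other sources, and the protocol's own data collection contradicts it.

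**Working it through.** The protocol states no cost, DALY or cost-effectiveness figure, so there is none to reproduce. The check sets the arm components beside the named cost inputs, then derives the direction of the error, then illustrates its size.

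**1. Components against inputs**

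| Item | Electronic arm | Paper arm | Named as a model cost |
|---|---|---|---|
| Staff time: training, tool use, supervision | yes | yes | yes, at wages |
| Staff time on the dashboard | yes | no | yes, as part of staff time |
| Paper guide | yes | yes | no, but roughly cancels |
| Phones and data packages for supervision | yes | yes | no, but roughly cancel |
| Clinic tablet | yes | no | no |
| App and dashboard hosting, maintenance, support | yes | no | no |

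The last two rows are in one arm only and in no list of inputs. Because the electronic arm keeps the paper guide, no printing saving offsets them within the trial.

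**2. Direction**

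Let F > 0 be the omitted electronic-only cost, ΔC the true incremental cost and ΔD the DALYs averted by the e-version relative to paper.

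- Reported incremental cost = ΔC − F.
- Net benefit of the e-version is overstated by F, whatever the sign of ΔD.
- If ΔD > 0, the reported cost per DALY is (ΔC − F)/ΔD, too low by F/ΔD.

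**3. Size, as an illustration for Nepal**

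Inputs from the protocol: about 20 clinics randomised 1:1, so 10 electronic-arm clinics (Statistical Power and Sample Size Calculation); about 200 patients screened per arm per month (Participants); 16.8% of primary care attendees with depression (Settings).

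Depressed patients screened per year in the electronic arm: 200 × 12 × 0.168 = 403.2.

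Assumptions, not in the protocol: a yearly tablet, app and dashboard cost of 50, 200 or 500 currency units per clinic, and a between-arm detection gain of 5, 10 or 20 points.

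Omitted cost per extra case detected = (10 × cost per clinic) / (403.2 × gain):

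| Gain | Extra cases | 50 per clinic | 200 per clinic | 500 per clinic |
|---|---|---|---|---|
| 5 points | 20.2 | 24.8 | 99.2 | 248.0 |
| 10 points | 40.3 | 12.4 | 49.6 | 124.0 |
| 20 points | 80.6 | 6.2 | 24.8 | 62.0 |

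The plan expects to screen about half of adult attendees. If the gain applied to all of them, positives would double to 806.4 and each entry would halve (3.1 to 124.0). Study Design gives 10 clinics per country instead of 20 in Nepal; with 5 electronic-arm clinics and the same patient numbers, each entry in the table would likewise halve. No figure is given for Nigeria, because its 5.5% prevalence is not stated to be for primary care attendees.

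**4. The patient-outcome sentence**

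Four places in the protocol conflict with it:

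- Objective 6 is to describe depression treatment outcomes.
- Patient Data under Implementation Data follows patients at about 3 months to measure those outcomes.
- Patient Data under Outcome Data schedules the PHQ-9 and WHODAS 2.0 at that visit and extracts treatment details.
- PCW and Patient Outcome Analysis assesses change in both scores.

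This part needs no assumption.

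**The case against.** The strongest reply is that silence is not exclusion. The protocol nowhere says that device or software costs are left out. Item 6 sits in a list of variables collected from PCWs in interviews, where a tablet price would not be expected. Health Economic Analysis describes a simple form of the model, a full cost inventory may stand in an analysis plan that is not at hand, and the Analysis section mentions costing data without defining them. A reader might infer that the tool's own cost is set to zero, or that all technology cost is deliberately excluded. The documents do not support that: staff time on the app and dashboard is counted, and there is no statement of exclusion. But the reply does not remove the point. Item 6 states how operating costs for the model will be derived, the economics section repeats the same basis, and the undefined costing data are tied to clinical feasibility, not to the model.

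Other parts of the reply stand:

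- Connectivity cannot be treated as purely electronic-arm cost. Data packages are provided for PCWs and supervisors without restriction to one arm, so at most a cost beyond those packages is missing.
- Nothing in the protocol shows that the app saves staff time. The extra dashboard training would raise the e-version's measured cost.
- No prices or decision threshold are given, so it cannot be shown that any conclusion would change.
- Economic modelling is not among the six objectives or the progression criteria, and the section claims only potential cost-effectiveness.

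On patient outcomes, a reader might infer that the model ought to use the trial's 3-month data. That goes too far. Neither scale gives DALYs directly. The model needs the improvement that results from detection, and the protocol describes the follow-up group in two ways: patients diagnosed by a health worker in one place, screen-positive patients in another. The first would leave no undetected comparator. Literature values may be a sound choice; only the reason given for them is wrong.

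**Conclusion.** The point holds in this form: the costing rule, followed as written, leaves the equipment and software cost of the e-version out of the incremental cost and so favours it. The direction follows from Table 1 and simple algebra, and rests only on that cost being greater than zero. The size cannot be determined from the protocol. The range of about 6 to 248 currency units per extra case detected depends entirely on assumed prices and detection gains, and the effect may be small once equipment is spread over its life and many patients. It is worth correcting before the model is built because the change is cheap and removes an error of known sign.

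The statement that patient outcomes are not measured is wrong on the protocol's own terms, independently of the costing point.

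**What to change.** In item 6 (Operating costs) and in Health Economic Analysis, define the cost of each tool as staff time valued at wages plus arm-specific resources: annualised tablets; app and dashboard hosting, maintenance and support; and any data cost beyond the packages already provided for supervision. Include these items in the planned sensitivity analysis.

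Replace the sentence saying that patient outcomes are not measured. State that PHQ-9, WHODAS 2.0 and treatment details are collected at 3 months and, if literature values are still preferred for the model, give the actual reason. Using the trial's own 3-month data as an added scenario is optional; if it is done, first reconcile the two descriptions of who is followed up.

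The cost is a little more costing work and a somewhat less favourable figure for the e-version. No trial procedure or patient data collection changes.
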